### 6.2 Secondary objective(s)

- To determine the clinical impact of Onpattro® use in adult patients with hATTR, in real world circumstances, in the Onpattro® subcohort in terms of Quality of Life (QOL), for the period starting from 01 July 2018 (start of EAP), up to 01 February 2021

For the endpoints of this survey, refer to Section 11.1.

## 7 SURVEY DESIGN

**Type of design:** Retrospective, multi-center, descriptive chart review.

**Survey groups:** single group without comparator.

**Mode of data collection:** Data collection form.

**Estimated survey period :** The questionnaire will cover the Onpattro® treatment period from 01 July 2018 to 1 February 2021. The survey will be performed between 01 April 2021 and 15 May 2021 (data collection between 01 April 2021 and 16 April 2021, and data analysis and report between 18 April 2021 and 15 May 2021).

An overview of the survey timelines is presented in Figure 1.

**Figure 1 Survey Timelines**

[figure not shown]

## 8 PATIENT POPULATION

The population will consist of adult patients ( $\geq 18$  years old) with hATTR confirmed by genetic testing, with stage 1 or stage 2 polyneuropathy.

### 8.1 Selection of the sites

Seven sites of NeuroMuscular Reference Centers (NMRC) in Belgium manage hATTR patients. It is estimated that approximately a total of 30 patients will be included from these 7 sites, of which approximately 9-12 patients treated with Onpattro® will be included in the Onpattro® sub-cohort. As 2 of the NMRC sites do not currently have patients treated with Onpattro®, only data for the total cohort will be collected for these sites. In the 5 remaining NMRC sites, data will be collected for the total cohort and the Onpattro® sub-cohort.

The 7 participating centers are as follows:

- Universitair Ziekenhuis (UZ) Leuven,
- Universitair Ziekenhuis Antwerpen (UZA),
- Universitair Ziekenhuis (UZ) Brussel,
- Universitair Ziekenhuis (UZ) Gent,
- Cliniques universitaires Saint-Luc (CuSL),
- Centre Hospitalier Régional (CHR) de la Citadelle,
- Hôpital Erasme - Cliniques universitaires de Bruxelles.

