**Secondary:**

QoL endpoints

- EQ5-D score
  - EQ5-D type
  - EQ5-D score
- SF-36 or SF-12 score (transformed to 0-100 scale; higher scores indicate better health-related QoL)

**Target population:** Adult patients with hATTR with polyneuropathy stage 1 or 2.

**Site selection and number:** 7 sites of NeuroMuscular Reference Centers (NMRC) in Belgium of which 5 sites currently have patients treated with Onpattro®.

**Sample size:** Approximately 30 patients in the total cohort (meeting the criteria for inclusion), of which approximately 9-12 patients treated with Onpattro®, in the Onpattro® sub-cohort.

**Inclusion & Exclusion criteria:** Adult patients (≥18 years old) diagnosed with hATTR with polyneuropathy, and confirmed by genetic testing will be included in this survey. There are no specific exclusion criteria.

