## CONFIDENTIAL AND PROPRIETARY

---

Sponsor name: Alnylam

Study ID: Onpattro® Survey

Protocol Version: 1.0

Data collection for the total cohort: the total number of patients by treatment (liver transplant, tafamidis, Onpattro®) will be collected as aggregated data.

Data collection for the Onpattro® subcohort: data for the Onpattro® subcohort will be collected as described in Table 1.

*Table 1 Data collected by timepoint for the Onpattro® subcohort*

| Parameters collected                                      | Timepoints                               |                        |                                            |                                        |
|-----------------------------------------------------------|------------------------------------------|------------------------|--------------------------------------------|----------------------------------------|
|                                                           | At EAP treatment initiation  | At first reimbursement | At reimbursement prolongation  | Last evaluation timepoint  |
| Age                                                       | X                                        | X          |                                            |                                        |
| Weight                                                    | X                                        | X                      | X                                          | X                                      |
| mBMI                                                      | X                                        | X                      | X                                          | X                                      |
| Treatment before Onpattro®                                | X                                        | X          |                                            |                                        |
| Onpattro® start date                                      | X                                        | X          |                                            |                                        |
| Prescribed dosage of Onpattro®                            | X                                        | X                      | X                                          | X                                      |

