| Echocardiography                                   | X                                        | X                      | X                                          | X                                      |
| QoL parameters                                     |                                          |                        |                                            |                                        |
| EQ5-D                                  | X                                        | X                      | X                                          | X                                      |
| SF-36 or SF-12                         | X                                        | X                      | X                                          | X                                      |

 for patients that were included in the EAP

 or no longer treated/still on initial reimbursement

 up to 01 February 2021, if available

 For patients not included in the EAP

 if available

 as defined by Coutinho (1980)

**CADT** - Compound Autonomic Dysfunction Test; **ECG** - Electrocardiogram; **EMG** - Electromyography; **FAP** - Familial Amyloid Polyneuropathy; **FIM** - Functional Independence Measurements; **mBMI** - Modified Body Mass Index; **MRC S-S** - Medical Research Council Sum-Score; **NIS** - Neuropathy Impairment Score; **NYHA** - New York Heart Association; **PND** - Polyneuropathy Disability; **QoL** - Quality of Life; **SF-36/12** - ShortForm 36/12; **VAS** - Visual Analog Scale.

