##### Onpattro Subcohort:

Onpattro® treatment use in terms of:

- Treatment start & stop dates (with reason for stopping)
- Prescribed dosage of Onpattro® (in mg/kg) at the beginning of each cycle
- Total number of Onpattro® vials consumed, at the end of each cycle
- Total number of Onpattro® treatment cycles
- Total number of Onpattro® vials at each timepoint (if available)

Onpattro® treatment compliance in terms of:

- Number of missed Onpattro® treatment cycles per year (if any)
- Treatment interruptions (if any), with dates of treatment discontinuation and treatment reinitiation (with reason for interrupting)

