**11.2 Cohorts**

The total cohort will include all patients meeting the inclusion criteria (i.e. with a diagnosis of hATTR confirmed by genetic testing), for which aggregated data will be collected.

The Onpattro® sub-cohort will include patients with hATTR that have been treated with Onpattro® from the start of the Expanded Access Program (EAP) in 01 July 2018, up to 01 February 2021, for which individualized data will be collected.

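### Sub-cohort data are collected only at sites with patients now on Onpattro, while the sub-cohort is defined as anyone treated in the window, so any former patients at the other two sites would be missed

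*Protocol*

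**What the plan says.** **Site rule.** Section 8.1 of the protocol names seven sites and separates two of them: "As 2 of the NMRC sites do not currently have patients treated with Onpattro®, only data for the total cohort will be collected". It continues: "In the 5 remaining NMRC sites, data will be collected for the total cohort and the Onpattro® sub-cohort". The synopsis describes the same split, seven sites "of which 5 sites currently have patients treated with Onpattro".

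**Cohort rule.** Section 11.2 reads: "The Onpattro® sub-cohort will include patients with hATTR that have been treated with Onpattro® from the start of the Expanded Access Program (EAP"), with start date 01 July 2018 and end date 01 February 2021. It requires neither that the patient is still on the drug nor that the patient belongs to particular sites. Section 8.2 lists no exclusion criteria.

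**Former patients are expected in the data.** The primary endpoints for the sub-cohort in Section 11.1.1 include "Treatment start & stop dates (with reason for stopping"). Table 1 in Section 9.2 has a treatment-stop row at all four timepoints. Its second footnote extends the reimbursement-prolongation timepoint to patients "or no longer treated/still on initial reimbursement".

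**What the two sites supply.** For the total cohort, Section 9.2 says "the total number of patients by treatment (liver transplant, tafamidis, Onpattro®) will be collected as aggregated data". Section 6.1 dates that count at 01 February 2021.

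**The concern.** Sites are selected on present use, while patients are defined by any use over 31 months. A site with no patient on the drug now can still have treated someone in the window. If it did, that patient is off the drug at that site, because the patient stopped, died or moved. So the site rule can remove only patients with an ended treatment course at those two sites. It cannot remove a patient who is still being treated there. Inclusion would then depend on something the survey reports as a primary endpoint.

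The stake is the description of persistence on treatment. Missed stoppers would make stopping look rarer. They would probably also make duration of use look longer. The report goes to the Belgian health insurer in connection with conditional reimbursement, and with an expected 9-12 patients a single omission is visible in any percentage.

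The word *currently* is also not tied to a date, so the rule does not say whether it means the end of the observation window, the date of the protocol or the time of data collection.

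**Working it through.** **1. The two rules side by side**

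| | Section 8.1 and synopsis | Section 11.2 |
|---|---|---|
| Unit | Site | Patient |
| Test | Has a treated patient now | Treated in the window |
| Time | *Currently*, undated | 01 July 2018 to 01 February 2021 |
| Sites | 5 of 7 | No restriction |

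The rules select the same patients if the two sites treated nobody in the window, or if everyone they treated is captured at one of the five. The protocol states neither.

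**2. Could another provision catch a missed patient?**

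- The aggregate count at the two sites carries no stop date, reason or clinical outcome. As it is dated 01 February 2021, a former patient would not be expected to appear in it under Onpattro.
- Section 9.2 provides for completeness checks and queries on the data collected, and for no source-document verification. A patient for whom no form is opened generates no query.
- Treatment data come from the site pharmacy, but the protocol does not ask the pharmacies for a list of everyone treated.

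No other provision captures former patients at the two sites.

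**3. Size**

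The protocol makes no power calculation and states no stop rate, so there is no figure of its own to reproduce. The following is a sensitivity calculation only.

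Inputs:
- n = patients captured at the five sites: 9 or 12, the expected range in Section 8.1.
- s = stoppers among those n: assumed 0 or 1.
- k = stoppers missed at the two sites: not given in the documents, assumed 0, 1 or 2.

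Formulas: reported share stopped = s / n; share with the missed patients included = (s + k) / (n + k).

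| n | s | Reported | k = 1 | k = 2 |
|---|---|---|---|---|
| 9 | 0 | 0/9 = 0% | 1/10 = 10.0% | 2/11 = 18.2% |
| 12 | 0 | 0/12 = 0% | 1/13 = 7.7% | 2/14 = 14.3% |
| 9 | 1 | 1/9 = 11.1% | 2/10 = 20.0% | 3/11 = 27.3% |
| 12 | 1 | 1/12 = 8.3% | 2/13 = 15.4% | 3/14 = 21.4% |

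With k = 0 the two formulas coincide and nothing changes. The s = 0 rows also give the share of the ever-treated cohort that would be missing, k / (n + k).

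**The case against.** The strongest reply is that the text of Section 8.1 fits two sites that have never used Onpattro just as well as two sites whose patients have stopped. On that reading *currently* is loose wording and the sub-cohort is complete. This stands as a limit: the documents do not settle it, so the loss is conditional.

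Three further points also stand:

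- **Stoppers at the five sites are covered.** The stop endpoint, the Table 1 rows and the footnote on patients no longer treated all apply there. A reader might infer that the survey drops treatment failures, withdrawals and deaths in general. It does not; the gap is confined to two of seven sites.
- **A transferred patient is not necessarily lost.** Someone who moved to one of the five sites meets Section 11.2 and can be included there.
- **The calculation rests on assumptions.** Both s and k are assumed. A stop rate is not itself a listed endpoint; the protocol lists dates and reasons and plans description only.

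A reader might also infer that every neurological and cardiac result is biased in the drug's favour. The documents do not support that. Reasons for stopping are unknown and need not be treatment failure, and nothing in the protocol allows the direction or size of an effect on those endpoints to be worked out.

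None of this removes the conflict between Sections 8.1 and 11.2. If the two sites never treated anyone, the protocol should say that.

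**Conclusion.** The point holds as an inconsistency with a conditional consequence. The site rule in Section 8.1 and the synopsis is narrower than the cohort definition in Section 11.2. It is narrower in a selective way, since the only patients it can remove are those whose treatment at the two sites has ended and who are not picked up at the other five.

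Whether anyone is affected is unknown. Assuming 1 or 2 missed stoppers, 9-12 patients captured and none of them stopped, the share stopped would be understated by 7.7 to 10.0 or 14.3 to 18.2 percentage points. If no such patient exists, the effect is zero and only the wording needs correcting. The conflict in the text is certain. The loss is possible. Any effect on neurological and cardiac outcomes is plausible but not demonstrated.

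**What to change.** 1. Reword Section 8.1 and the synopsis so that the site rule follows Section 11.2, for example: *Sub-cohort data are collected at every site that treated at least one patient with Onpattro between 01 July 2018 and 01 February 2021, whether or not the patient is still treated.*
2. Have all seven site pharmacies, already the source of treatment data under Section 9.2, confirm the list of patients treated in that window, or confirm that there are none.
3. Report, out of all ever-treated patients, how many stopped, died, transferred or objected to the use of their data.

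If the two sites confirm that they treated nobody, no further forms are needed and Section 8.1 can state that fact.

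**Cost.** Both sites already take part, so the extra data work is a pharmacy check and, under the assumption used here, one or two forms. The procedural cost is larger. Section 12.2 requires a written amendment approved by the sponsor and the ethics committee. Any added patient moves from aggregate to individual data, so the written information and right to object in Section 12.3 apply. That section does not say how this works for a patient who has died, and the amendment should settle it. All of this has to be in place before the collection window of 01-16 April 2021.

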## 8.2 Inclusion/exclusion criteria for patients

Inclusion criteria: adult patients ( $\geq 18$  years old) with a diagnosis of hATTR with polyneuropathy, confirmed by genetic testing.

Exclusion criteria: there are no specific exclusion criteria.

# 9 DATA MANAGEMENT

## 9.1 Patient identification

Each patient will be given a unique number to maintain data confidentiality when the patient is included in the survey and is retained as the primary identifier for the patient throughout the survey's duration. Pseudonymized data (anonymous to non-site staff) from patients' medical records will be recorded in the data collection form.

## 9.2 Data collection

Data recorded in patients' medical records from 01 July 2018 up to 01 February 2021 (observation period) will be collected by site personnel using a data collection form developed by Modis Life Sciences. A data entry assistant from Modis will be available to help record data on the data collection form, upon request by the investigator. Onpattro® treatment data will be obtained from the NMRC site pharmacy.

No personal identifiable information will be collected. After the data entry will be finalized, data will be exported in a format that will allow for data analysis. The sponsor will receive anonymized individual data.

No source-document verification will be performed. Throughout the survey, data management will conduct a verification of completeness of the data and a verification of any inconsistencies in collected data. In case of missing or inconsistent data, queries will be sent to the site for correction.

## CONFIDENTIAL AND PROPRIETARY

---

Sponsor name: Alnylam

Study ID: Onpattro® Survey

Protocol Version: 1.0

Data collection for the total cohort: the total number of patients by treatment (liver transplant, tafamidis, Onpattro®) will be collected as aggregated data.

Data collection for the Onpattro® subcohort: data for the Onpattro® subcohort will be collected as described in Table 1.

*Table 1 Data collected by timepoint for the Onpattro® subcohort*

| Parameters collected                                      | Timepoints                               |                        |                                            |                                        |
|-----------------------------------------------------------|------------------------------------------|------------------------|--------------------------------------------|----------------------------------------|
|                                                           | At EAP treatment initiation  | At first reimbursement | At reimbursement prolongation  | Last evaluation timepoint  |
| Age                                                       | X                                        | X          |                                            |                                        |
| Weight                                                    | X                                        | X                      | X                                          | X                                      |
| mBMI                                                      | X                                        | X                      | X                                          | X                                      |
| Treatment before Onpattro®                                | X                                        | X          |                                            |                                        |
| Onpattro® start date                                      | X                                        | X          |                                            |                                        |
| Prescribed dosage of Onpattro®                            | X                                        | X                      | X                                          | X                                      |
| Number of Onpattro® vials                                 |                                          | X          | X                                          | X                                      |
| Onpattro® treatment stop (with date and reason)           | X                                        | X                      | X                                          | X                                      |
| Onpattro treatment interruption (with date and reason)    | X                                        | X                      | X                                          | X                                      |
| Onpattro® reinitiation                        |                                          |                        | X                                          | X                                      |
| Number of cycles                                          |                                          | X                      | X                                          | X                                      |
| Neurological parameters                                   |                                          |                        |                                            |                                        |
| Polyneuropathy and FAP stage  (if applicable) | X                                        | X                      | X                                          | X                                      |
| NIS score                                                 | X                                        | X          | X                              | X                          |
| EMG                                                       | X                                        | X                      | X                                          | X                                      |
| MRC S-S                                                   | X                                        | X                      | X                                          | X                                      |
| FIM score                                                 | X                                        | X                      | X                                          | X                                      |
| Activity limitations (measured by ACTIVLIM)   | X                                        | X                      | X                                          | X                                      |

CONFIDENTIAL AND PROPRIETARY

Sponsor name: Alnylam

Study ID: Onpattro® Survey

Protocol Version: 1.0

| Parameters collected                               | Timepoints                               |                        |                                            |                                        |
|----------------------------------------------------|------------------------------------------|------------------------|--------------------------------------------|----------------------------------------|
|                                                    | At EAP treatment initiation  | At first reimbursement | At reimbursement prolongation  | Last evaluation timepoint  |
| CADT                                   | X                                        | X                      | X                                          | X                                      |
| VAS score for pain                     | X                                        | X                      | X                                          | X                                      |
| Polyneuropathy disability (PND) score  | X                                        | X                      | X                                          | X                                      |
| Cardiological parameters                           |                                          |                        |                                            |                                        |
| Orthostatic hypotension                            | X                                        | X                      | X                                          | X                                      |
| NYHA score                                         | X                                        | X                      | X                                          | X                                      |
| ECG                                                | X                                        | X                      | X                                          | X                                      |
| Echocardiography                                   | X                                        | X                      | X                                          | X                                      |
| QoL parameters                                     |                                          |                        |                                            |                                        |
| EQ5-D                                  | X                                        | X                      | X                                          | X                                      |
| SF-36 or SF-12                         | X                                        | X                      | X                                          | X                                      |

 for patients that were included in the EAP

 or no longer treated/still on initial reimbursement

 up to 01 February 2021, if available

 For patients not included in the EAP

 if available

 as defined by Coutinho (1980)

**CADT** - Compound Autonomic Dysfunction Test; **ECG** - Electrocardiogram; **EMG** - Electromyography; **FAP** - Familial Amyloid Polyneuropathy; **FIM** - Functional Independence Measurements; **mBMI** - Modified Body Mass Index; **MRC S-S** - Medical Research Council Sum-Score; **NIS** - Neuropathy Impairment Score; **NYHA** - New York Heart Association; **PND** - Polyneuropathy Disability; **QoL** - Quality of Life; **SF-36/12** - ShortForm 36/12; **VAS** - Visual Analog Scale.

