**11.3 Planned analyses**

The analysis of the collected information will only consist of descriptive data such as frequencies, aggregated averages, standard deviations and ranges. No formal statistical analysis plan is set out, neither has there been any statistical hypothesis formulated. The final report of this survey will consist of a descriptive presentation of the collected data.

This is an observational survey and only data collected in routine clinical practice will be used. Only data available at the time of the survey are to be recorded, hence no substitution,

imputation, or other correction methods will be used to complete missing values. Statistical analyses will only be performed on parameters collected in sufficient numbers.

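### NIS is availability-only after EAP initiation and section 11.3 states no paired summary, so NIS averages at different timepoints may describe different patients

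*Protocol*

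**What the plan says.** Protocol section 11.1.1 lists NIS (0-244) among the primary neurological endpoints. Table 1 in section 9.2 sets its collection as "NIS score | X | X 5 | X 5 | X 5". The columns are EAP initiation, first reimbursement, reimbursement prolongation and last evaluation. Footnote 5 is "5 if available".

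Three other footnotes matter:

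- The EAP-initiation column applies only "1 for patients that were included in the EAP".
- Age, prior treatment and Onpattro start date are taken at first reimbursement under "4 For patients not included in the EAP". That column is thus the starting point for patients who did not come through the EAP.
- The whole last-evaluation column carries "3 up to 01 February 2021, if available".

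Section 9.2 adds: "In case of missing or inconsistent data, queries will be sent to the site for correction". Section 8.1 expects that "approximately 9-12 patients treated with Onpattro® will be included in the Onpattro® sub-cohort".

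Section 11.3 describes the analysis as descriptive data such as "frequencies, aggregated averages, standard deviations and ranges". It uses only what routine practice recorded, rules out imputation, limits analysis to parameters with sufficient numbers (not defined), and says that no formal statistical analysis plan has been laid down.

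**The concern.** Among the clinical scores, NIS is the only row in which the availability footnote sits on some timepoints and not on others. ACTIVLIM, CADT, VAS, PND, EQ5-D and SF-36/12 carry it on the row label, so it applies equally throughout. EMG, MRC S-S and FIM do not carry it. No reason is given for treating NIS differently.

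The set of patients with a NIS can therefore change from column to column for two reasons. First, the score is expected at EAP initiation and optional later. Second, the first column holds EAP patients only, while later columns can also hold patients who started outside the EAP, and for them even the treatment-start NIS is optional.

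NIS serves the primary objective on clinical impact, and the results go to the Belgian Health Insurance Agency. A difference between two timepoint averages is easily read as improvement or worsening on Onpattro. In a group this small, part or all of it could come from who was measured.

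**Working it through.** The protocol gives no NIS standard deviation, no expected availability and no power calculation, so there is no planned figure to reproduce. The check asks how far the averages could move if no patient's NIS changed at all.

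**Inputs from the protocol:** 9-12 treated patients (section 8.1); available-data averages without imputation (section 11.3); first column limited to EAP patients (Table 1, footnote 1).

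**Assumptions not in the protocol:** between-patient SD of NIS 20 to 40 points; the numbers re-measured and the numbers from the EAP, as shown below.

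**1. Later scores missing at random.** With n patients at the start, m of them scored later and no true change, the later average minus the start average has mean 0 and

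SD of shift = SD × √(1/m − 1/n).

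| n | m | √(1/m − 1/n) | SD 20 | SD 40 |
|---|---|---|---|---|
| 10 | 6 | 0.258 | 5.2 | 10.3 |
| 12 | 9 | 0.167 | 3.3 | 6.7 |
| 12 | 6 | 0.289 | 5.8 | 11.5 |
| 9 | 6 | 0.236 | 4.7 | 9.4 |
| 9 | 4 | 0.373 | 7.5 | 14.9 |

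At SD 30, 6 of 10 gives 30 × 0.258 = 7.7 points.

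**2. Availability related to severity.** In 100,000 simulated cohorts with n = 12 and m = 6, a correlation of 0.5 between severity and availability gives an average shift of 7.5 points (SD 20) to 15.0 points (SD 40). In the extreme case, where only the six most severe patients have a later score, it is 15.0 to 29.9 points. The shift is upward if the more severe patients are re-measured. By symmetry it is downward by the same amount if the less severe are. For 6 of 10, with only the least severe re-measured, it is −0.59 SD, or about −12 to −24 points. These are bounds on a mechanism, not forecasts.

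**3. EAP mix alone.** Suppose NIS is complete at both timepoints, but only e of the n patients were in the EAP, and EAP and non-EAP patients do not differ systematically. The move from the EAP-initiation average to the first-reimbursement average then has SD = SD × √(1/e − 1/n). For n = 12:

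- e = 6: 5.8 to 11.5 points
- e = 11: 1.7 to 3.5 points

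**4. Paired summary.** If each patient's later score is compared with that patient's own starting score, every difference is 0 under no true change. The mean change is then exactly 0 in all the scenarios under 1 and 2, whichever patients are missing. The mix in 3 drops out as well, because each patient is compared only with himself or herself. Real scores carry measurement error, so observed paired changes would vary around 0, but not because the set of patients changed.

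**The case against.** Several points on the other side are sound.

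- **Retrospective data.** The observation period ended on 01 February 2021 and forms are completed in April 2021. Whether NIS was measured is already settled, so the footnote does not create missing scores. A query can recover a score that was recorded but not transcribed, and nothing more. This stands and limits what changing Table 1 can achieve.
- **Last evaluation.** Footnote 3 makes every parameter availability-only in that column. NIS is therefore not distinctive in a comparison of EAP initiation with last evaluation. Its separate treatment is confined to first reimbursement and prolongation.
- **Wording of section 11.3.** It lists types of summary and does not say that unpaired averages will be compared. The subcohort data are individual, so pairing is possible, and such detail is often left to an analysis plan. Against this, section 11.3 itself says that no formal plan is set out, and nothing in the protocol commits to pairing. The condition on sufficient numbers is some protection, but it is undefined and does not address which patients are averaged.

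A reader might also infer more than the protocol supports:

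- That EAP initiation supplies a full set. It covers EAP patients only, and in a chart review an unqualified mark means expected, not guaranteed.
- That blank later NIS values will not be chased. The query sentence in section 9.2 exempts no item. The footnote only makes it possible to accept a blank.
- That the more disabled patients will be the ones without a later NIS, so that the drift imitates benefit. The protocol gives no reason for missing scores, and the direction is unknown.

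**Conclusion.** The point holds as a modest one. The inconsistency in Table 1 is real, concerns a primary endpoint and is unexplained. Together with available-data averages and no stated pairing, it means that NIS averages at different timepoints may rest on different patients. With 9-12 treated patients, the apparent shift under no true change has an SD of roughly 5 to 10 points when 6 of 10 are re-measured at random. It could be larger if availability is related to severity. The EAP-only first column can produce a shift of similar size even with complete NIS.

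All sizes depend on an assumed between-patient SD of 20 to 40 and on assumed availability. If nearly every patient has a NIS at each timepoint and nearly all came through the EAP, the effect is small. The documents do not support a claim that the averages will differ by construction, or that they will be biased in favour of Onpattro.

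**What to change.** **Section 11.3 (the main change).** Summarise NIS as within-patient change from each patient's own Onpattro start, taken at EAP initiation or, for patients not in the EAP, at first reimbursement. Include only patients with both values. Show the paired number beside the number treated at each timepoint. State that differences between unpaired timepoint averages will not be read as clinical impact.

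**Table 1.** Make NIS an expected, queried item at first reimbursement and prolongation, as it is at EAP initiation, so that recorded but untranscribed scores are recovered. Marking NIS as optional in all four columns would also remove the inconsistency, but would recover nothing.

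**Cost.** One sentence or two in section 11.3, one footnote change in Table 1 and a few more queries. The paired summary will use fewer patients than the start average. Scores that were never measured cannot be recovered. Pairing removes the effect of a changing set of patients, but does not show that the paired patients represent the whole subcohort, which is why the two numbers should appear side by side.
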